### Population and procedures

The population in this study consists of adult partners of cancer patients. To receive a heterogeneous group of participants, a multi-component recruitment strategy is followed (see Table 3). In all recruitment materials (e.g. advertisements, leaflets) the URL of the website (www.houvastvoorelkaar.nl) is mentioned, where respondents can find more information (including a short promotion video) and where they can apply to participate. On this website respondents can also read and download the patient information letter. Respondents can also do a self-assessment of eligibility on basis of the in- and exclusion criteria. Inclusion criteria are: (1) age of 18 years and older; (2) being partner of a cancer patient or cancer survivor; (3) having internet access; (4) no problems with the Dutch language; (5) and having mild to moderate symptoms of psychological distress symptoms (>3 on the Hospital Anxiety and Depression Scale (HADS) [25]. Exclusion criteria are: (1) severe anxiety (score on HADS-A ≥ 15) and severe depression (score on HADS-D ≥ 15); (2) recently started (less than three months ago) with psychological or psychopharmacological treatment; (3) not being able to spend 1-1.5 hours on the intervention every week; (4) partner died because of cancer and (5) diagnosis of partner’s disease is less than 3 months ago. Respondents who are eligible and would like to participate in the study can fill out an online contact form and will then receive an informed consent form by mail (reply envelope included). Respondents are asked to return the signed informed consent within a few days by mail.

**Table 3 Tab3:** **Recruitment channels and recruitment strategies**

**Recruitment via**	**Recruitment strategy**
• National newspapers and magazines	Advertisements, newspaper articles
• Media	Interviews on radio and television, Twitter, Facebook
• Websites and magazines of relevant organizations (e.g. website of Dutch Cancer Society)	Online advertisements, newsletters
• Patient organizations and drop-in-centers	Online advertisements, newsletters, leaflets, presentations
• Hospitals and psycho-oncological organizations	Online advertisements, newsletters, leaflets, posters, presentations
• Other (e.g. psychologists, rehabilitation centers, general practitioners, physiotherapists)	Leaflets, posters

After receiving this informed consent, participants are sent an invitation by e-mail to fill out the HADS (14 items). People with severe anxiety and/or depression (cut-off score ≥ 15 on HADS-A and/or ≥ 15 HADS-D) [26] are excluded, because severe distress would require more intensive individual diagnostics and treatment. Participants that are excluded based upon severe psychological distress are contacted by telephone by a psychologist in order to be sure that these people are referred to adequate help. All partners with moderate scores on HADS-A and/or HADS-D (score 11-14 on HADS-A and/or HADS-D) are telephoned to assess the depressive episode module and the anxiety disorder modules of the Mini International Neuropsychiatric Interview (M.I.N.I.) [27]. In people screened as having a depressive disorder and/or an anxiety disorder by the MINI, the Sheehan Disability Scale (SDS) [28,29] is administered to measure the severity of their symptoms. Participants are asked to rate the extent to which work, social life and family life are impaired by their symptoms on a 10 point scale (0 = not at all impaired; 10 = extremely impaired). If participants report on at least two areas of their life severe impairment (scores ≥ 7) [28], they will be excluded from the study and will be strictly referred to seek adequate professional help. The telephone assessment of the M.I.N.I will be performed by trained and supervised master students.

### Randomization

Respondents who are eligible, have provided their informed consent, and have completed the baseline (T0) questionnaire, are automatically randomized and divided over the three conditions. Randomization is stratified for gender, so an equal distribution of female and male participants in all conditions is warranted. Additionally we stratify for the perceived stage of disease, which is measured by the following item: (1) My partner is still in treatment and we have good hope that he/she will recover; (2) The treatment is completed and we are moving on with our lives; (3) My partner is unlikely to be cured. All participants receive an e-mail with the outcome of randomization and a link to start the intervention. Participants are informed about the three different conditions. They know that there is a waiting list control condition and that there are two experimental versions, one with automatic feedback and another with personal feedback. Participants in the experimental conditions will receive immediate access to the web-based intervention *Hold on, for each other*. The intervention is individually administered and the participants can access the intervention at any time, from any place, free of charge. Participants that will be placed on a waiting list have the opportunity to access treatment as usual (TAU) and they will be referred to relevant websites such as the website of Dutch Cancer Society (http://www.kwfkankerbestrijding.nl/ or http://www.kanker.nl) for information. Three months after the baseline measurement, which is directly after the first follow-up measurement at three months, participants on the waiting list receive the opportunity to follow the web-based intervention *Hold on, for each other* with automated feedback. They will also be invited to fill out measurements 6 and 12 months after the baseline measurement (see flowchart, Figure 1).

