#### Outcome measures

*Psychological distress*—the primary outcome—is measured with the total Hospital Anxiety and Depression Scale (HADS) [25]. The HADS is a 14-item questionnaire that measures the presence and severity of anxiety and depressive symptoms. Answering categories range from 0 to 3 and the items are added to a scale score that can range from 0 – 42. Higher scores mean more symptoms of psychological distress.

*Mental health* is assessed with the Mental health Continuum – Short Form (MHC-SF) [30,31]. The MHC-SF is a 14-item questionnaire that measures three dimension of positive mental health [30]: emotional well-being (3 items), psychological well-being (6 items), and social well-being (5 items). Participants are asked to rate the frequency of feelings they have experienced in the past month. Items are scored on a 6-point scale ranging from 1 to 6. A mean score is computed ranging from 1 to 6 with higher scores indicating higher levels of positive mental health. The Dutch version of the MHC-SF has shown good psychometric properties [31].

*Caregiver strain* is assessed with the 13-item Caregiver Strain Index (CSI) [32]. The CSI contains at least one item to measure burden in each of the following major domains: employment, financial, physical, social and time. Each item can be answered with ‘yes’ (1) or ‘no’ (0). A CSI score is computed by counting the number of ‘yes’, resulting in a score from 0-13. The CSI has shown good psychometric properties [32].

*General health* of the partners of cancer patients is assessed with one item of the RAND 36 [33,34]. This item “How would you rate your own general health?” can be answered on a 5-point scale ranging from 1 - 5, with higher scores indicating better general health.

*Health-related quality of life* of the participants is measured with the EuroQol EQ-5D [35]. The EQ-5D is a validated instrument for measuring health-related quality of life and it covers five domains of health: mobility, self-care, usual activity, pain/discomfort and depression/anxiety. Each of the five domains has three severity levels; 0 (none), 1 (some), and 2 (severe).

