#### Effects

One-way ANOVA’s and χ^2^-tests will be performed to see if there are no significant differences at baseline between the two conditions for any of the demographic variables or outcome measures. Non-significant differences will indicate successful randomization. Intention-to-treat analyses will be conducted with use of SPSS missing values analysis to impute all missing data on the continuous measuring multiple imputation methods in SPSS. To examine differences between the conditions on all outcome measures, ANOVA (group x time) will be used. In the case of significant group x time – interactions, Tukey’s post hoc tests will be used.

Effect sizes on the primary outcome variable (HADS total) at post-intervention will be calculated with Cohen’s D using the means and pooled standard deviations of the measurements of the conditions (effect size of above .56 are considered large, .33-.55 are considered moderate, and less than .33 are considered as small [51].

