#### Moderation and mediation analysis

The moderating effect of the socio-demographics (age, gender, education, working situation, family situation) and disease-related characteristics of the patients (type of cancer, stage of disease, duration and treatment of cancer) on the effectiveness of the intervention will be analyzed using regression analyses.

Mediation analysis will be performed as described by Preacher and Hayes [52,53]. Aim of this analysis is to assess whether psychological flexibility, self-compassion, supportive behavior, posttraumatic growth and resilience are mediators in the effect between the independent variable and the dependent variables.

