### Sample size calculation

Based upon a previous, similar study [54] we expect effect sizes of at least d = 0.5. To demonstrate the presence of an effect of at least d = 0.5 as statistically significant in a two-tailed test at alpha = 0.05 and a power of (1-beta) = 0.80, a minimum of 64 participants in each condition will be required at follow-up (power calculation in G*Power). We have extended our sample size with 5 participants per condition in order to take normal distribution of the data as well as possible post hoc tests into account. Anticipating a drop-out rate of 20% between T0-measurement and T3-measurement, at least 87 participants per condition need to be included at T0-measurement. The total study cohort comprises thus 261 participants.

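### The group x time ANOVA uses baseline HADS only as a repeated measurement and leaves out the stratification factors; adjusting for both would gain precision at no cost

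*Protocol article*

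**What the plan says.** Under Randomization, people who "have completed the baseline (T0) questionnaire, are automatically randomized and divided over the three conditions". Allocation has two stratification factors. For the first: "Randomization is stratified for gender, so an equal distribution of female and male participants in all conditions is warranted". For the second: "Additionally we stratify for the perceived stage of disease", recorded with a three-option item.

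Table 4 lists HADS total, the primary outcome, at T0, T1, T2 and T3 in every arm.

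Under Effects, the analysis model is: "To examine differences between the conditions on all outcome measures, ANOVA (group x time) will be used". Tukey tests follow a significant interaction. The section names no covariate or stratification factor, and does not say which time points enter the ANOVA. Baseline values are otherwise used there only to test whether the arms differ at the start.

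The same section adds: "Effect sizes on the primary outcome variable (HADS total) at post-intervention will be calculated", as Cohen's d from means and pooled standard deviations.

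Gender and stage appear as analysis variables only under Moderation and mediation analysis, where moderation "on the effectiveness of the intervention will be analyzed using regression analyses".

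**The concern.** Three things that the design already supplies are not used to estimate the treatment effect as well as they could be.

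- **Baseline HADS.** In a group x time ANOVA it is one more level of the outcome. With T0 and T1 only, the interaction is the comparison of mean changes. That fixes the coefficient on baseline at 1 instead of estimating it, which costs precision whenever r is below 1.
- **Gender and stage.** Allocation is balanced on them, but the model that estimates the effect does not contain them.
- **The effect size.** The test concerns change, while Cohen's d compares raw post-intervention means. If the arms differ at baseline by chance, the two can give different impressions of the primary result.

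What is at stake is precision and one coherent primary estimate. The protocol's own discussion of limitations expects recruitment to be hard, so precision that needs no extra participants is worth having.

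**Working it through.** **1. The plan's own figure.** Inputs from Sample size calculation: "we expect effect sizes of at least d = 0.5", two-sided alpha 0.05, power 80%. A two-sample t-test needs 63.77, so 64 per arm. Adding 5 gives 69. Allowing for 20% drop-out, 69/0.80 = 86.25, so 87 per arm, and 3 × 87 = 261. The stated figures reproduce. Power of that plain t-test at 69 per arm is 83.0%.

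**2. Variance under each analysis.** Work in units of the HADS variance, with equal SDs at T0 and T1, and with d = 0.5 on the T1 SD:

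- T1 scores alone: 1
- T0-T1 group x time (change score): 2(1 − r)
- ANCOVA on T0: 1 − r²
- ANCOVA / change = (1 − r²) / [2(1 − r)] = (1 + r)/2

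**3. Power and sample size.** The effective standardised difference is 0.5/√variance. The settings are 69 per arm, one pairwise contrast and unadjusted two-sided alpha 0.05. The document does not give r, so the table covers an assumed range.

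| r (assumed) | Variance, change | Variance, ANCOVA | Ratio | Power, change | Power, ANCOVA | n per arm for 80%, change / ANCOVA |
|---|---|---|---|---|---|---|
| 0.3 | 1.40 | 0.91 | 0.65 | 69.3% | 86.4% | 89 / 59 |
| 0.4 | 1.20 | 0.84 | 0.70 | 75.9% | 88.9% | 77 / 54 |
| 0.5 | 1.00 | 0.75 | 0.75 | 83.0% | 92.0% | 64 / 49 |
| 0.6 | 0.80 | 0.64 | 0.80 | 90.3% | 95.4% | 52 / 42 |
| 0.7 | 0.60 | 0.51 | 0.85 | 96.4% | 98.3% | 39 / 34 |
| 0.8 | 0.40 | 0.36 | 0.90 | 99.6% | 99.8% | 27 / 24 |

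A simulation of 2000 trials per setting agrees. Change against ANCOVA was 83.1% and 92.5% at r = 0.5, 90.1% and 95.4% at 0.6, and 96.7% and 98.5% at 0.7.

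Below r = 0.5 the change score has variance above 1, so it is less precise than the plain comparison that produced 64 per arm.

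**4. Strata.** Suppose gender and stage explain a share R² of the variance left after baseline; R² is assumed to be 0.02 to 0.10. The variance becomes (1 − r²)(1 − R²). At r = 0.5 this is 0.735 to 0.675. The n per arm for 80% power falls from 49 to between 48 and 44, and power at 69 per arm is 92.5% to 94.4%.

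**5. Test against effect size.** Let D0 and D1 be the between-arm differences at T0 and T1. The test uses D1 − D0 and Cohen's d uses D1, so they differ by exactly D0. With 69 per arm the standard error of D0 is √(2/69) = 0.17 SD. A chance imbalance of one standard error therefore separates the two by 0.17 SD, against a planned effect of 0.5 SD. ANCOVA uses D1 − r·D0, which lies between them.

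**The case against.** The strongest reply is that both analyses are valid, so this is a preference about efficiency. Baseline is not ignored: as a repeated level it already removes stable differences between people. The size of the gain rests on an r that the article does not give, and at r = 0.8 it is about 0.2 percentage points. The time points are also not stated. If all four enter with three arms, the interaction has (3 − 1)(4 − 1) = 6 degrees of freedom and the percentages above do not describe it. A fuller analysis plan might add covariates. Cohen's d is descriptive and, under randomisation, has the same expectation as the tested difference.

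Most of this stands and limits the point. It does not remove it: the article names its model, and in a group x time ANOVA baseline is an outcome level and not a covariate, whichever time points are used.

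Three stronger readings are tempting but unsupported.

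- **That power is already below the stated 80%.** At unadjusted alpha 0.05 the T0-T1 change test has 83% power or more for r of 0.5 and above. It falls below 80% only when 63.77 × 2(1 − r) exceeds 69, that is, for r under about 0.46. The article does not say that r is that low.
- **That omitting stage inflates the standard error because stage predicts distress.** A stable effect of stage or gender on the level of distress cancels within each person's change. In a simulation with stage shifting HADS by 0.6 SD in either direction at both visits, the standard error was 0.170 with or without stage. Omission costs precision in the change score only if stage predicts change.
- **That stage was stratified because it predicts distress.** The article gives a reason for gender, equal distribution across conditions, and none for stage.

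**Conclusion.** The point holds as a free improvement to the model stated under Effects. Read as a T0-T1 comparison, the planned ANOVA has a larger variance than baseline-adjusted ANCOVA at every r below 1. The avoidable part of its variance is (1 − r)/2: 35% at r = 0.3, 25% at 0.5 and 15% at 0.7. In power per contrast the gain is about 17 points at r = 0.3, 9 at 0.5 and 2 at 0.7.

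These figures assume equal SDs at T0 and T1, d = 0.5 on the T1 SD, 69 evaluable per arm and no multiplicity adjustment. The direction is certain; the size is not, because r is not given. The extra gain from gender and stage is probably modest.

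Nothing here shows bias or an invalid test, and the sample size of 261 stands on its own inputs. The mismatch between the change-based test and the unadjusted Cohen's d is a lesser matter of chance imbalance, and the same change resolves it.

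**What to change.** Under Effects, replace the group x time ANOVA as the primary analysis with a linear model for T1 HADS total containing:

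- arm, with each intervention version contrasted with the waiting list;
- T0 HADS total;
- gender;
- perceived stage, three levels.

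Pool coefficients over the multiply imputed datasets. Use the same form for the other continuous outcomes, each with its own baseline value. T1 is the natural time point because the waiting list receives the intervention directly afterwards.

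Report the adjusted mean difference with its 95% confidence interval, and compute the standardised effect size from that difference, so that test, estimate and effect size answer one question.

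The cost is analysis wording only. HADS, gender and stage are all recorded before allocation, and no participants, visits or questionnaires are added. The planned sample size need not change.

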**Figure 1 Fig1:**
[figure not shown]
**Flowchart of ‘Hold on, for each other’.**

### Measurements

#### Overview

Table 4 gives an overview of all measurements. Participants will be asked to complete online questionnaires at baseline (T0); three months after the baseline measurement (T1); six months after the baseline measurement (T2); and twelve months after the baseline measurement (T3). The intervention as well as the questionnaires can be worked through in the participant’s own living environment.

**Table 4 Tab4:** **Measurement overview**

		**Experimental conditions**				**Control condition**			
**Measure**	**Instrument**	**T0**	**T1**	**T2**	**T3**	**T0**	**T1**	**T2**	**T3**
*Socio-demographics and disease-related characteristics*									
Socio-demographics of the partner	Sex, age, education, marital status, cultural background, children, work status	X				X			
Disease-related variables of the patient	Sort of cancer, time of diagnosis, past and current treatment, current situation (prognosis)	X				X			
*Outcome measures*									
Psychological distress	HADS total	X	X	X	X	X	X	X	X
Mental health	MHC-SF	X	X	X	X	X	X	X	X
Caregiver strain	CSI	X	X	X	X	X	X	X	X
General health	RAND 36	X	X	X	X	X	X	X	X
Health-related quality of life	EuroQol EQ-5D								
*Mediators*									
Psychological flexibility	AAQ-II	X	X	X	X	X	X	X	X
Self-compassion	SCS-SF	X	X	X	X	X	X	X	X
Posttraumatic growth	PTGI-SF	X	X	X	X	X	X	X	X
Resilience	BRS	X	X	X	X	X	X	X	X
Sense of mastery	Pearlin Mastery Scale	X	X	X	X	X	X	X	X
Support behavior	Active engagement scale	X	X	X	X	X	X	X	X
*Evaluation*									
Client satisfaction	CSQ-8		X					X	
Evaluation form			X					X	
*Economic evaluation*									
Healthcare consumption	TiC-P	X			X	X			X
Production loss due to illness and absenteeism	PRODISQ	X			X	X			X
*Screening* ^*1*^									
Depression/anxiety (optional screening)	MINI (part: A, B, C, D, E, F, G, H, I, J, P)	X				X			
Severity of symptoms	SDS	X				X			

^1^The MINI and SDS will only be administered in people who have moderate scores on HADS-A and/or HADS-D (score 11 - 14 on HADS-A and/or HADS-D).

#### Socio-demographics and disease-related characteristics

The following socio-demographics of the partners are assessed: sex, age, education, marital status, cultural background, children, work status. Regarding their partner’s disease, participants are asked about type of cancer, time since diagnosis, current treatment and self-reported stage of disease (see description in paragraph ‘Randomization’).

#### Outcome measures

*Psychological distress*—the primary outcome—is measured with the total Hospital Anxiety and Depression Scale (HADS) [25]. The HADS is a 14-item questionnaire that measures the presence and severity of anxiety and depressive symptoms. Answering categories range from 0 to 3 and the items are added to a scale score that can range from 0 – 42. Higher scores mean more symptoms of psychological distress.

*Mental health* is assessed with the Mental health Continuum – Short Form (MHC-SF) [30,31]. The MHC-SF is a 14-item questionnaire that measures three dimension of positive mental health [30]: emotional well-being (3 items), psychological well-being (6 items), and social well-being (5 items). Participants are asked to rate the frequency of feelings they have experienced in the past month. Items are scored on a 6-point scale ranging from 1 to 6. A mean score is computed ranging from 1 to 6 with higher scores indicating higher levels of positive mental health. The Dutch version of the MHC-SF has shown good psychometric properties [31].

*Caregiver strain* is assessed with the 13-item Caregiver Strain Index (CSI) [32]. The CSI contains at least one item to measure burden in each of the following major domains: employment, financial, physical, social and time. Each item can be answered with ‘yes’ (1) or ‘no’ (0). A CSI score is computed by counting the number of ‘yes’, resulting in a score from 0-13. The CSI has shown good psychometric properties [32].

*General health* of the partners of cancer patients is assessed with one item of the RAND 36 [33,34]. This item “How would you rate your own general health?” can be answered on a 5-point scale ranging from 1 - 5, with higher scores indicating better general health.

*Health-related quality of life* of the participants is measured with the EuroQol EQ-5D [35]. The EQ-5D is a validated instrument for measuring health-related quality of life and it covers five domains of health: mobility, self-care, usual activity, pain/discomfort and depression/anxiety. Each of the five domains has three severity levels; 0 (none), 1 (some), and 2 (severe).

#### Moderators and mediators

In this study age, gender, stage of disease and compliance (frequency and time spend on the website) are examined as moderators. The following variables are examined as mediators: psychological flexibility, self-compassion, posttraumatic growth, resilience, styles of support behavior and sense of mastery.

*Psychological flexibility* is measured with the 7-item Acceptance and Action Questionnaire II (AAQ-II) [36,37]. Answering categories range from 1 to 7 and the items are added to a scale score that can range from 7 to 49, with higher scores indicating more psychological flexibility [36]. The Dutch version of the AAQ-II has shown good psychometric properties [38] also in adults with psychological distress [39].

*Self-compassion* is measured with the Self-compassion Scale Short-Form (SCS-SF) [40,41]. This questionnaire consists of 12 items and is measuring six components of self-compassion: self-kindness, self-judgment, common humanity, isolation, mindfulness and over-identification (2 items for each component). Respondents rate on a 7-point scale ranging from 1 to 7. A mean score is computed with higher scores indicating higher levels of self-compassion. The SCS-SF has adequate psychometric properties [41].

*Posttraumatic growth* is assessed with the 10-item Posttraumatic Growth Inventory- Short Form (PTGI-SF) [42,43]. All items are positively formulated and comprising five factors: (1) relation to others (2 items); (2) new possibilities (2 items); (3) personal strength (2 items); (4) spiritual change (2 items); and (5) appreciation of life (2 items). Respondents rate each item on a 6- point scale ranging from 0 to 5 and the items are added to a scale score that can range from 0 - 50, higher scores indicating higher posttraumatic growth. The questionnaire has shown good psychometric properties [43].

*Resilience* is measured with the 6-item Brief Resilience Scale (BRS) [44]. The BRS assesses the ability to bounce back or recover from stress. Respondents rate on a 5-point scale ranging from 1 to 5. The BRS is scored by averaging the scores on the items (after reversing the negative ones). The score can range from 1 to 5, higher scores indicating higher levels of resilience. The BRS has shown good psychometric properties [44].

*The different styles of support behavior* are assessed with the 19-item Active engagement scale [45]. Five items constitute the active engagement scale, 8 items measure protective buffering and 6 items measure overprotection. Items can be answered on a 5-point scale ranging from 1 to 5. For each subscale, the items are averaged within subjects into a scale score that ranges from 1 - 5. The Active engagement scale has shown good psychometric properties [46].

*Sense of mastery* is measured with the 5-item Pearlin Mastery Scale (PMS) [47]. The instrument measures the extent to which one regards one’s life chances as being under one’s own control in contrast to being fatalistically ruled. Items are scored on a 5-point scale from 1 to 5. The scores on the items are added to a sum score that can vary from 5 to 25. High scores signify that the individual perceives him or herself in control of his or her life.

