### Present study

This present study has several aims. First, we want to assess the (cost-)effectiveness of the intervention *Hold on, for each other*. Our main hypothesis is that both versions of the intervention lead to a significant reduction of psychological distress compared to a waiting list control condition. In addition, we hypothesize that (positive) mental health, health related quality of life and general health of participants of the experimental conditions will increase and caregiver burden will decrease in comparison to the participants in the waiting list control condition. The second aim of our study is to examine if psychological flexibility, self-compassion, mastery, style of support behavior (overprotection, protective buffering, active engagement), posttraumatic growth and resilience are mediators of the intervention’s effects on the partners’ mental health. Third, we aim to examine the moderating effects of the socio demographics (age, gender, education, working situation, family situation) and disease-related characteristics of the patients (sort of cancer, stage of disease, duration and treatment of cancer). Finally, we want to know to what extend participants are satisfied with the intervention, which parts of the intervention are mostly used, and how compliant the users are.

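### Website compliance is listed as a moderator although it arises after randomisation, and the moderator and mediator lists differ between sections

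*Protocol article*

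**What the plan says.** **Moderators.** The section *Moderators and mediators* states: "In this study age, gender, stage of disease and compliance (frequency and time spend on the website) are examined as moderators". The statistical section *Moderation and mediation analysis* gives a different set: "The moderating effect of the socio-demographics (age, gender, education, working situation, family situation) and disease-related characteristics of the patients", with the disease items and method following as "type of cancer, stage of disease, duration and treatment of cancer) on the effectiveness of the intervention will be analyzed using regression analyses". *Present study* sets out that same longer set as an aim: "we aim to examine the moderating effects of the socio demographics (age, gender, education, working situation, family situation) and disease-related characteristics of the patients". The Abstract and the opening of the Discussion repeat it. None of these four places lists compliance as a moderator.

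**Mediators.** *Moderators and mediators* names "psychological flexibility, self-compassion, posttraumatic growth, resilience, styles of support behavior and sense of mastery". *Present study* begins its list with "psychological flexibility, self-compassion, mastery, style of support behavior". The analysis paragraph, however, sets out to assess "whether psychological flexibility, self-compassion, supportive behavior, posttraumatic growth and resilience are mediators in the effect", with no mention of mastery.

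**Timing and access.** *Randomization* places allocation after the T0 questionnaire and access after allocation. *Study design* and *Randomization* keep the waiting list without access until after T1, then offer it the automated version. The description of the intervention says that the counsellor's e-mails serve mainly to improve adherence.

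**The concern.** To ask whether a variable modifies a treatment effect, one compares the randomised contrast across levels of something that allocation could not have changed. Website use fails that test. It follows allocation, people on the waiting list cannot have any before T1, and one active arm is designed to increase it. People who use a self-help site more may also differ in motivation or distress from those who use it less. A positive finding could then be presented as the programme working better in those who use it more, when it reflects who those people are.

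The differing lists are a second problem. A reader cannot tell from *Moderators and mediators* and the analysis section together which moderator set is planned, or whether mastery is to be tested as a mediator.

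**Working it through.** **1. Moderator lists side by side**

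| Moderator | Moderators and mediators | Abstract, Present study, Moderation and mediation analysis, Discussion |
|---|---|---|
| Age | yes | yes |
| Gender | yes | yes |
| Stage | yes | yes |
| Compliance | yes | no |
| Education | no | yes |
| Work | no | yes |
| Family | no | yes |
| Cancer type | no | yes |
| Duration | no | yes |
| Treatment | no | yes |
| **Total** | **4** | **9** |

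Shared: 3. Only in the short list: 4 − 3 = 1 (compliance). Only in the long list: 9 − 3 = 6. Apart from compliance, the short list is a subset of the long one. Table 4 schedules the socio-demographic and disease variables at T0 only, so the nine are baseline variables.

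**2. Mediator lists**

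*Moderators and mediators* has six, counting styles of support as one. The analysis paragraph has five. The difference, 6 − 5 = 1, is mastery. Mastery is named as a mediator in the Abstract, *Present study*, *Moderators and mediators* and the Discussion. Table 4 places it under mediators at T0 to T3 in all conditions. That is five places against one.

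**3. Active arm against waiting list, up to T1**

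Let a = 1 for an active arm and a = 0 for the waiting list, and let u be website use. The usual moderation model is

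y = b0 + b1·a + b2·u + b3·(a × u) + error.

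- Waiting list: u = 0 for everyone, so a × u = 0 = u.
- Active arm: a = 1, so a × u = u.

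The columns u and a × u are therefore identical, and the model matrix has rank 3 of 4. Only the sum b2 + b3 can be estimated. It is the slope of outcome on use within the active arm, not a difference in treatment effect.

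**4. The other comparisons**

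- *Personal against automated support.* Use varies in both arms, so the interaction can be fitted. Use is still post-randomisation, and personal support is intended to shift it. Participants with equal use in the two arms are not a randomised comparison.
- *After T1.* The waiting list may then use the automated version, so its use could be logged. No unexposed control remains, and *Strengths and limitations of the RCT* acknowledges the lack of long-term control data.

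**5. Illustration with assumed values**

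The article gives no correlation between use and prognosis, so a range was assumed. The simulation had 2,000 runs, one active arm and a waiting list of 87 each, a true effect of d = 0.5 and no true moderation. The use term was significant at the 5% level in:

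| Assumed correlation of use with prognosis | Runs significant |
|---|---|
| 0 | 4.7% |
| 0.3 | 79% |
| 0.5 | 100% |

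The direction of the spurious slope follows the sign of the assumed correlation. This shows the mechanism only and is not an estimate for this trial.

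**6. Sample size**

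The stated figures reproduce. A two-sided t-test with d = 0.5, alpha 0.05 and power 0.80 needs 63.77 per arm, so 64. Then 64 + 5 = 69; 69 / 0.80 = 86.25, so 87; and 3 × 87 = 261. No moderator or mediator enters this calculation.

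**The case against.** The strongest reply is that the paragraph specifying the moderation analysis does not include compliance. Anyone following it runs nine baseline moderators and no analysis by use. The Abstract and *Present study* place adherence or compliance with satisfaction and component use, as a separate aim. *Strengths and limitations of the RCT* puts time on the website in the process evaluation. On this reading, one sentence in the measurement section is out of line with an otherwise coherent plan. That reply largely stands, and it limits several inferences that a reader might draw:

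- *That the trial will report a better effect in heavier users.* This follows only if the one sentence is acted on. The analysis section does not call for it.
- *That the interaction can never be estimated.* The article states no model, comparison or time point for compliance. Non-identifiability holds for active against waiting list up to T1. Between the active arms the difficulty is causal interpretation.
- *That mastery will not be analysed.* One omission against five statements shows an inconsistency, probably a drafting slip. It does not show that the test was dropped.
- *That the moderator set is wide open to choice after the data are seen.* The nine-item list is the same in four places, and three of the four short-list entries lie within it.

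The reply does not remove the sentence itself. It says that compliance is examined as a moderator, and condensing the longer list could not have produced an entry that the longer list lacks.

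**Conclusion.** The point holds in limited form. An analysis of compliance as a moderator, as *Moderators and mediators* states it, would give a confounded association in every comparison available: not separable from the main effect of use against the waiting list up to T1, affected by the allocated support between the active arms, and without an unexposed control after T1. This rests on the article's own order of events and stated purpose of the counsellor contact, not on the simulated rates.

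The inconsistencies are one moderator entry that four other places do not have, six entries missing from that same sentence, and one mediator missing from the analysis paragraph. The analyses concerned are additional goals. The primary comparison on total HADS and the 261 participants do not depend on them. The text should be corrected, but the trial's main conclusion is not at risk from this point.

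**What to change.** 1. In *Moderators and mediators*, delete compliance and replace the sentence with the nine baseline moderators, so that it matches the Abstract, *Present study*, *Moderation and mediation analysis* and the Discussion.
2. Report website frequency and time as process data. If a relation with outcome is shown, restrict it to the active arms and label it a non-causal dose-response description. This fits the existing adherence aim and process evaluation.
3. Add mastery to the mediators in *Moderation and mediation analysis*.

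A complier-average estimate is not needed to settle this point. It would require a cut-off for use, and people below the cut-off would still receive some modules and feedback, which strains the exclusion restriction.

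The cost is wording only. Mastery is already scheduled at all four time points, time on the website is already part of the process evaluation, and no new measure or participant is required.
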